**Session-4**

**Common triggers of Intimate partner violence**

- Alcohol use
- Drug abuse
- Ongoing anxiety of infidelity
- Mental health problems(depression, anxiety)
- Infidelity accusation
- Sexual jealousy

How to solve /minimize the triggers of intimate partner violence during pregnancy

- Avoid/minimize alcohol or alcohol use
- Talk things over-properly

If either of the partner has mistrust or misinformation, talk it over

Speak calmly, openly and honestly

- Don’t force things

It is not healthy to impose your beliefs on another person

Bring the trigger on the table and talk it over

- Don’t blame
- Make your relationship a priority
- Be honest to your partner
- Don’t lie
- Don’t dig up old wound
- Respect your partner’s boundary
- Don’t be jealous
- Be a good listener

**Session -6 women empowerment**

**Empowerment**: empowerment means that both women and men –can take control over their lives: set their agendas, gain skills (or have their own skills and knowledge recognized), increase self-confidence, solve problems, and develop self-reliance”

**Empowering women**: is ensuring that women participate fully in social, political and economic life.

When individuals are better able to make strategic choices in their lives, it has consequences for their economic and social well-being

Importance of empowering women

- - Effect of effective empowering of women
  - Free from violence
  - Have control on sexual and reproductive rights
  - Can get their voice herd
  - Have social and economic mobility
  - Have the ability to own and control financial assets
  - Have control over their income

**Ways of empowering women**

- End all forms of discrimination against all women and girls everywhere.
- Eliminate all forms of violence against all women and girls in the public and private spheres, including trafficking and sexual and other types of exploitation.
- Eliminate all harmful practices, such as child, early and forced marriage and female genital mutilation.
- Recognize and value unpaid care and domestic work through the provision of public services, infrastructure and social protection policies, and the promotion of shared responsibility within the household and the family
- Ensure women’s full and effective participation and equal opportunities for leadership at all levels of decision-making in political, economic and public life.
- Ensure universal access to sexual and reproductive health and reproductive rights
- Undertake reforms to give women equal rights to economic resources, as well as access to ownership and control over land and other forms of property, financial services,
- Expanding women education services

**Annex VI: የአማርኛ መጠይቅ (የምስት)**

**መልሱን የያዘውን ፊደል በማክበብ ምረጡ ወይንም ክፍት ቦታውን የምሰጡትን ምላሽ በመጻፍ አሟሉ**

| **ክፍል አንድ፡ የግለሰብ፣ ግንኙነት፣ የማህበረሰብ እና የማህበረሰብ ደረጃ መጠይቆች** | | | |
| --- | --- | --- | --- |
| መለያ  ቁጥር | ጥያቄዎች | አማራጭመልስ | እለፍ |
| 101 | አሁን ዕድሜዎ ስንት ነዉ? | ሙሉ ዓመት…………….……… |  |
| 102 | ወደ ጋብቻ ስገቡ ዕድሜዎ ስንት ነበር? | ሙሉ ዓመት በቁጥር……………. |  |
| 103 | የሚኖሩበት ቦታ የት ነዉ? | ገጠር……………………………………….…1  ከተማ…………………………………………2 |  |
| 104 | ከተጋቡ ምን ያህል ዓመት ቆይተዋል? | ሙሉ ዓመት………………………………..1  አላዉቅም----------------------------------2 |  |
| 105 | የባሎት ዕድሜ ስንት ነዉ? | ሙሉ ዓመት _________________ |  |
| 106 | ሀይማኖትዎ ምንድነዉ? | ጴንጤ.................................................................1  ኦርቶዶክስ.........................................................2  ሙስሊም...............................................................3  ካቶሊክ..... ........................................................4  ሌላ ይገለጽ............................................................5 |  |
| 107 | የባሎት ሀይማኖት ምንድነዉ? | ኦርቶዶክስ.............................................................2  ሙስሊም.........................................................3  ካቶሊክ..... ............................................................4  ሌላ, ይገለጽ........................................................5 |  |
| 108 | ብሄሮት ምንድነዉ ነዉ? | ሀዲያ.................................................................1 ክምባታ...........................................................2  ስልጤ................................................................3  ጉራጌ.................................................................4  ሌላ, ይገለጽ......................................................5 |  |
| 109 | የባሎት ብሄር ምንድነዉ ነዉ? | ሀዲያ.................................................................1 ክምባታ...........................................................2  ስልጤ................................................................3  ጉራጌ.................................................................4  ሌላ, ይገለጽ......................................................5 |  |
| 110 | የትምህርት ደረጃዎት ስንት ነው? | ትምህርት የለም.................................................1  አንደኛ ደረጃ ትምህርት ቤት (1-8)......................2  ሁለተኛ ደረጃ ት/ቤት (9-12)………………..….3  ኮሌጅ ወይም ከፍተኛ ትምህርት ተከታትሏል …...4 |  |
| 111 | የባሎት የትምህርት ደረጃ ስንት ነዉ? | ትምህርት የለም.................................................1  አንደኛ ደረጃ ትምህርት ቤት (1-8)......................2  ሁለተኛ ደረጃ ት/ቤት (9-12)………………..….3  ኮሌጅ ወይም ከፍተኛ ትምህርት ተከታትሏል …...4 |  |
| 112 | ሥራዎት ምንድን ነው? | የቤት እመቤት ...................................................1  የመንግስት ተቀጣሪ...........................................2  የግል ስራ………………….……………….......3  ሌላ, ይገለጽ......................................................5 |  |
| 113 | የባሎት ስራ ምንድን ነዉ? | ገበሬ.................................................................1  የመንግስት ተቀጣሪ...........................................2  የግል ስራ………………….……………….......3  ሌላ, ይገለጽ......................................................5 |  |
| 114 | የትዳር አጋርዎ/ባልዎ በአሁኑ ጊዜ ሲጋራ ያጨሳል? | አዎ……………..…………………………......1  አይደለም………………………………….......2 |  |
| 115 | ባሎት/የትዳር አገርዎ በአሁኑ ጊዜ አረቄ /ቢራ ይጠጣል? | አዎ……………..…………………………......1  አይደለም………………………………….......2 |  |
| 116 | ባሎት ስንት ምስት አለዉ? | አንድ ………………………….……….……..1  ሁለትና ከዚያ በላይ………………….……........2 |  |
| **ክፍል ሁለት፡-ቤት እና ንብረትን የሚመለከቱ ጥያቄዎች** | | |  |

| 201 | የሚኖሩበት ቤት የተሰራው ከምንድን ነው? | | | | | 1.ከቆርቆሮ ክዳን | | | | 2.ከሳር ክዳን | | |  | |
| --- | --- | --- | --- | --- | --- | --- | --- | --- | --- | --- | --- | --- | --- | --- |
| 202 | የተለየ ምኝታ ክፍል አለዎት? | | | | | 1.አዎ | | 2.የለም | |  | | |  | |
| 203 | ለጥያቄ ቁ.202 መልሱ አዎ ከሆነ ስንት ክፍል? | | | | | 1.አንድ | | 2. ሁለት | | 3. ሶስት | | |  | |
| 204 | ከዋናው ቤት የተለየ የእንስሳት ቤት አለዎት? | | | | | 1.አዎ | | 2.የለም | |  | | |  | |
| 205 | ከዋናው ቤት የተለየ ማብሰያ ቤት አለዎት? | | | | | 1.አዎ | | 2.የለም | |  | | |  | |
| 206 | ከቤተሰብ አባላት ላም ያለው አለ? | | | | | 1.አዎ | | 2.የለም | | አዎ ካሉ ስንት-- | | |  | |
| 207 | ከቤተሰብ አባላት በሬ ያለው አለ? | | | | | 1.አዎ | | 2.የለም | | አዎ ካሉ ስንት-- | | |  | |
| 208 | ከቤተሰብ አባላት ጥጃ ያለው አለ? | | | | | 1.አዎ | | 2.የለም | | አዎ ካሉ ስንት-- | | |  | |
| 209 | ከቤተሰብ አባላት ከላይ ከተዘረዘሩት ሌላ ከብት ያለው አለ?(ጊደር፤ ወይፈን) | | | | | 1.አዎ | | 2.የለም | | አዎ ካሉ ስንት-- | | |  | |
| 210 | ከቤተሰብ አባላት ፈረስ ያለው አለ? | | | | | 1.አዎ | | 2.የለም | | አዎ ካሉ ስንት-- | | |  | |
| 211 | ከቤተሰብ አባላት አህያ ያለው አለ? | | | | | 1.አዎ | | 2.የለም | | አዎ ካሉ ስንት-- | | |  | |
| 212 | ከቤተሰብ አባላት በቅሎ ያለው አለ? | | | | | 1.አዎ | | 2.የለም | | አዎ ካሉ ስንት-- | | |  | |
| 213 | ከቤተሰብ አባላት በግ ያለው አለ? | | | | | 1.አዎ | | 2.የለም | | አዎ ካሉ ስንት-- | | |  | |
| 214 | ከቤተሰብ አባላት ፍየል ያለው አለ? | | | | | 1.አዎ | | 2.የለም | | አዎ ካሉ ስንት-- | | |  | |
| 215 | ከቤተሰብ አባላት ዶሮ ያለው አለ? | | | | | 1.አዎ | | 2.የለም | | አዎ ካሉ ስንት-- | | |  | |
| 216 | ከቤተሰብ አባላት ንብ ያለው አለ? | | | | | 1.አዎ | | 2.የለም | | አዎ ካሉ ስንት ቀፎዎች-- | | | |  |
| 217 | ከቤተሰብ አባላት መሬት ያለው አለ? | | | | | 1.አዎ | | 2.የለም | | አዎካሉ ስንትሄክታር--- | | | |  |
| 218 | ከቤተሰብ አባላት ሬድዮ ያለው አለ? | | | | | 1.አዎ | | 2.የለም | | አዎ ካሉ ስንት-- | | | |  |
| 219 | ከቤተሰብ አባላት ቴሌዠን ያለው አለ? | | | | | 1.አዎ | | 2.የለም | | አዎ ካሉ ስንት-- | | | |  |
| 220 | ከቤተሰብ አባላት ሞባይል ያለው አለ? | | | | | 1.አዎ | | 2.የለም | | አዎ ካሉ ስንት-- | | | |  |
| 221 | ከቤተሰብ አባላት የምግብ ጠረምጴዛ ያለው አለ? | | | | | 1.አዎ | | 2.የለም | | አዎ ካሉ ስንት-- | | | |  |
| 222 | ከቤተሰብ አባላት ሶፋ ወንበር ያለው አለ? | | | | | 1.አዎ | | 2.የለም | | አዎ ካሉ ስንት-- | | | |  |
| 223 | ከቤተሰብ አባላት ባለእስፖንጅ ፍራሽ አልጋ ያለው አለ? | | | | | 1.አዎ | | 2.የለም | | አዎ ካሉ ስንት-- | | | |  |
| 224 | ከቤተሰብ አባላት የሶላር መብራት ያለው አለ? | | | | | 1.አዎ | | 2.የለም | | አዎ ካሉ ስንት-- | | | |  |
| 225 | ከቤተሰብ አባላት ስዓት ያለው አለ? | | | | | 1.አዎ | | 2.የለም | | አዎ ካሉ ስንት-- | | | |  |
| 226 | ከቤተሰብ አባላት ብስክሌት ያለው አለ? | | | | | 1.አዎ | | 2.የለም | | አዎ ካሉ ስንት-- | | | |  |
| 227 | ከቤተሰብ አባላት ሞተር ያለው አለ? | | | | | 1.አዎ | | 2.የለም | | አዎ ካሉ ስንት-- | | | |  |
| 228 | ከቤተሰብ አባላት ጋሪ ያለው አለ? | | | | | 1.አዎ | | 2.የለም | | አዎ ካሉ ስንት-- | | | |  |
| 229 | ከቤተሰብ አባላት የባንክ ደብተር ያለው አለ? | | | | | 1.አዎ | | 2.የለም | | አዎ ካሉ ስንት-- | | | |  |
| 230 | ከቤተሰብ አባላት የጫት ማሳ ያለው አለ? | | | | | 1.አዎ | | 2.የለም | | አዎ ካሉ ስንት ሄክታር-- | | | |  |
| 231 | ከቤተሰብ አባላት የባህር ዛፍ ማሳ አለ? | | | | | 1.አዎ | | 2.የለም | | አዎ ካሉ ስንት ሄክታር-- | | | |  |
| **የሚከተሉትን እህል፤ ጥራጥሬ፤አትክልት እና ፍራፍሬዎች በዚህ አመት ምን ያህል እንዳመረቱ ጠይቁ** | | | | | | | | | | | | | | |
| 233 | ጤፍ-ኩ/ል | ዳጉሳ--ኩ/ል | | በቆሎ--ኩ/ል | ስንዴ--ኩ/ል | | ገብስ--ኩ/ል | | | | አጃ--ኩ/ል | ሩዝ--ኩ/ል | | |
| 234 | ባቄላ--ኩ/ል | አተር--ኩ/ል | | ምስር--ኩ/ል | ለውዝ--ኩ/ል | | ሽምብራ-ኩ/ል | | | | ጓያ--ኩ/ል | ሌላካለ ይጠቀስ---- | | |
| 235 | ጎመን--ኪ.ግ | | ካሮት--ኪ.ግ | | ድንች--ኪ.ግ | | | | ቲማቲም--ኪ.ግ | | | ጥቅልጎመን--ኪ.ግ | | |
|  | ቀይ ሽንኩርት--ኪ.ግ | | ነጭሽንኩርት--ኪ.ግ | | ቀይ ስር--ኪ.ግ | | | | ዱባ--ኪ.ግ | | | በርበሬ--ኪ.ግ | | |
| 236 | ማንጎ--ኪ.ግ | | ሙዝ--ኪ.ግ | | አቦካዶ--ኪ.ግ | | | | ፓፓያ--ኪ.ግ | | | ዘይቱና-ኪ.ግ | | |
|  | ሎሚ--ኪ.ግ | | ሌላ ካለ ይጠቀስ---- | | | | | | | | | | | |

|  | **ክፍል ሶስት፡ የቅርብ ጊዜ ቅድመ ወሊ እና ወሊድ እና በተመለከተ** | | | | | | | | | | | | |
| --- | --- | --- | --- | --- | --- | --- | --- | --- | --- | --- | --- | --- | --- |
| 301 | እስካሁን ስንት በህይወት ያለዉን ልጅ ወልደዋል(ስንት ጊዜ ወልደዋል) | | በቁጥር………………………………. | | | | | | | | | |  |
| 302 | ከዚህ በፊት ለነበረዉ የቅርብ ጊዜ እርግዝና የቅድመ ወሊድ ክትትል አድርገዉ ነበር? | | አዎ………………………….……………..….1  አይደለም…………………………….………..2 | | | | | | | | | | አይደለም  ከሆነ ወደ  **305 እለፊ** |
| 303 | የቅድመ ወሊድ ክትትል አድርገዉ ከሆነ ከየትኛዉ የጤና ተቋም ነዉ ስከታተሉ የነበረ? | | ሆስፕታል…………………….……………..….1  ጤናጣቢያ.…………………….…………..…..2  ክሊኒክ…………………….………………..….3  ጤና ኬላ--------------------------------…...------4  ሌላይገለጽ.…………………….…………..…..5 | | | | | | | | | |  |
| 304 | ላለፈው እርግዝና ወቅት ባሎት/የትዳር አጋርዎ ከእርስዎ ጋር የቅድመወሊድ ሲያደርጉ ከርሶ ጋር አብር ወደ ጤና ተቋም ሄዶ ያዉቃል ? | | አዎ……………………………….….…………1  አይደለም……………………………………….2 | | | | | | | | | |  |
| 305 | በቅርብ እርግዝና ወቅት በእርግዝና ወቅት የአደጋ ምልክቶች አጋጥሞ ያዉቃል ? | | አዎ……………………………….……………1  አይደለም…………………………………...….2 | | | | | | | | | |  |
| 306 | የቅርብ ልጅዎን የት ነው የወለዱት? | | ቤት…………………………………...………...1  ሆስፕታል…………………...………...………...2  ጤናጣቢያ…………………..………...……......3  ክሊኒክ.………………………………...…..…...4  ጤና ኬላ---------------------------------------5 | | | | | | | | | |  |
| 307 | ሆስስፕታል ወይም ጤና ጣቢያ ወይም ክሊኒክ ወይም ክሊኒክ ከሆነ የቅርብ ልጅዎን ስወልዱ ፣ባለቤቶት/የትዳር አጋሪዎ አብሮ ነበር? | | አዎ-------------------------------------------------------…1  አይደለም-------------------------------------------------2 | | | | | | | | | |  |
|  | **ክፍል አራት ፡ የአሁኑ እርግዝና በተመለከተ** | | | | | | | | | | | |  |
| 401 | የአሁኑን እርግዝና  ለማርገዝ ፈልገህ ነበር?  እስከ በኋላ ድረስ መጠበቅ ፈልገህ ነበር ? ወይስ  ምንም (ተጨማሪ) ልጅ መውለድ አይፈልጉም ነበር? | | ፈልጌ ነዉ …………..……………...…..…….....1  ከተወሰ ጊዜ በኋላ ነበር መርገዝ እፈልግ ነበር……..2  ማርገዝ ምንም አልፈልግም ነበር…………….….3 | | | | | | | | | |  |
| 402 | ለአሁኑ እርግዝናዎ የቅድመ ወሊድ ክትትል ከሰለጠኑ የጤና ባለሙያዎች (ከነርስ፣ አዋላጅ፣ ዶክተር ወይም የጤና መኮንን) ተገኝተዋል? | | አዎ……….……………………….……………1  አይደለም……………………………………….2 | | | | | | | | | | 2 አየደለም  ከሆነ ወደ 405 እለፊ |
| 403 | አዎ ከሆነ፣ የት ነዉ የቅድሚያ ወሊድ የተከታተሉት? | | ሆስፕታል……….……………………….……1  ጤናጣቢያ……….……………………….…..2  ክሊኒክ.......................................................3  ጤና ኬላ----------------------------…]-----------4  ሌላ, ይገለጽ.........................................................5 | | | | | | | | | |  |
| 404 | ለአሁኑ እርግዝና የልጅዎ አባት ከእርስዎ ጋር የቅድመ-ወሊድ ጉብኝት ተካፍሏል? | | አዎ……….……………………….……………1  አይደለም……………………………………….2 | | | | | | | | | |  |
| 405 | አሁን ባለው እርግዝና ወቅት በእርግዝና ወቅት የሚከሰቱ የጤና አደጋ ምልክቶችን አስተውለዋል? | | አዎ……….……………………….……………1  አይደለም……………………………………….2 | | | | | | | | | |  |
| 406 | በአሁኑ እርግዝና ላይ በነበሩበት ወቅት ሴትን ምን አይነት የጤና ችግሮች አጋጥሞወታል? ከአንድ በላይ ምልክት ሊደረግባቸው ይችላል (ምላሾችን አያነብቡ) | | አዎ አይደለም  በእርግዝና ወቅት በማህጸን  ከባድ የደም መፍሰስ...................1 2  እጆች / ፊት እብጠት................1 2  ከባድ ራስ ምታት....................1 2  የፅንስ እንቅስቃሴ አለመኖር........1 2  የደበዘዘ እይታ........................1 2  በወሊድ ጊዜ እና ልጅ በሚወልዱበት  ጊዜ ከባድ በማህጸን ደም መፍሰስ.1 2  ለረጅም ጊዜ የሚቆይ ሚጥ  መንቀጥቀጥ.............................1 2  እራስን መሳት ………………...1 2 | | | | | | | | | |  |
| 407 | ከዚህ እርግዝና በፊት የተወለደዉ ህጻን ጾታ ምንድነዉ? | | ወንድ………………………………………….1  ሴት……………………………..……………..2 | | | | | | | | | |  |
|  | **ክፍል አምስት : የሴቶች ራስን በራስ የማስተዳደር እና ማህበራዊ ድጋፍ** | | | | | | | | | | | |  |
| 500 | **የሴቶች በራሳቸዉ የመወሰን መጠይቅ** | | | | | | | | | | | |  |
|  | በሚከተሉት የቤት ዉስጥ ጉዳዮች ላይ የመጨራሻ ዉሳኔ ሰጪማን ነዉ?  1.ሚስትብቻ 2. ባልብቻ 3. ባልና ምስት አንድላይ 4 ሌላ ሰዉ/ የቤተብ አባል | | |  | | | | | | | | |  |
| 501 | ትናንሽ እና ትላልቅ ግዢዎችን ጨምሮ በቤተሰብ ግዢዎች ላይ? | | | 1 | 2 | | 3 | | | | 4 | |  |
| 502 | ዘመዶችን እና ጓደኞችን ለመጎበኛት? | | | 1 | 2 | | 3 | | | | 4 | |  |
| 503 | የሚስቱን ገቢ ወጪ በማድረግ? | | | 1 | 2 | | 3 | | | | 4 | |  |
| 504 | የሚወልዱ ልጆች ብዛት? | | | 1 | 2 | | 3 | | | | 4 | |  |
| 505 | ለእርስዎ የጤና እንክብካቤ ለማገኘት? | | | 1 | 2 | | 3 | | | | 4 | |  |
| 506 | **ማህበራዊ ድጋፍ** | | | | | | | | | | | |  |
| 507 | ምን ያህል ሰዎች ከእርስዎ ጋር በጣም ቅርብ ስለሆኑ ታላቅ የግል ችግሮች ካጋጠሙዎት በእነሱ ላይ መተማመን ይችላሉ? | | | የለም...................................................1  1–2.....................................................2  3–5.....................................................3  5+......................................................4 | | | | | | | | |  |
| 508 | ሰዎች በምታደርገው ነገር ምን ያህል ፍላጎት እና አሳቢነት ያሳያሉ? | | | ምንም………………………………1  ትንሽ……………………..……...…...2  እርግጠኛ አይደለሁም...........…………3  የተወነ……………….…………...…..4  ብዙ………………….………………5 | | | | | | | | |  |
| 509 | ከፈለጉ ከጎረቤቶች ተግባራዊ እርዳታ ማግኘት ምን ያህል ቀላል ነው? | | | በጣም ከባድ …...………………..…1  ከባድ…………..………….…………2  ይቻላል…………………..…..………3  ቀላል…………………….………...…4  በጣም ቀላል…..….………….………5 | | | | | | | | |  |
|  | **ክፍል ስድስት : የእውቀት፣ የአመለካከት እና የባህሪ መቆጣተር ጥያቄዎች** | | | | | | | | | | | |  |
| 600 | **እዉቀት** | | | | | | | | | | | |  |
| 601 | ስለ የቅርብ አጋር ጥቃት ሰምተዉ ያዉቃሉ? | | | አዎ ……………………….1  አላዉቅም----------------2 | | | | | | | | |  |
| 602 | የቅርብ አጋር ጥቃት ላይ የመረጃ ምንጮች ሚዲያ፣ሆስፕታል፣ጤና ጣቢያ ፣ጤና ጣቢያ ወዘተ..ናቸዉ? | | | አዎ ……………………….1  አላዉቅም----------------2 | | | | | | | | |  |
| 603 | የቅርብ አጋር( ጥቃት የህዝብ ጤና ጉዳይ ነው። | | | አዎ ………………………………….1  አይደለም……………..……………..2 | | | | | | | | |  |
| 604 | በጥፊ መምታት፣ መምታት፣ መጎተት፣ መደብደብ፣ ማነቅ፣ መግፋት፣ ወዘተ.የፍቅር አጋር ጥቃት ምሳሌዎች ናቸው። | | | አዎ ………………………………….1  አይደለም……………..……………..2 | | | | | | | | |  |
| 605 | ባልፈለገች ጊዜ ወሲብ እንዲፈጽም ማስገደድ ወሲባዊ ጥቃት ነው። | | | አዎ ………………………………….1  አይደለም……………..……………..2 | | | | | | | | |  |
| 606 | እሱ/እሷ የሚያዋርድ ወይም የሚያዋርድ ነገር እንዲፈጽም ማስገደድ ወሲባዊ ጥቃት ነው። | | | አዎ ………………………………….1  አይደለም……………..……………..2 | | | | | | | | |  |
| 607 | አጋርን በሌሎች ሰዎች ፊት ማዋረድ ወይም ማዋረድ የስነ-ልቦና ጥቃት ነው። | | | አዎ ………………………………….1  አይደለም……………..……………..2 | | | | | | | | |  |
| 608 | በእርግዝና ወቅት የቅርብ ወዳጃዊ ጥቃት የእናቶች እና አዲስ የሚወለዱ ሕፃናት ላይ አሉታዊ ውጤቶች አሉት፡፡ | | | አዎ ………………………………….1  አይደለም……………..……………..2 | | | | | | | | |  |
| 609 | የቅርብ አጋር /የትዳር አጋር ጥቃት የሰብአዊ መብት ጥሰት ነው። | | | አዎ …………………………….…….1  አይደለም……………..………..……..2 | | | | | | | | |  |
| 610 | **የአመለካከት ጥያቄዎች** | | | | | | | | | | | |  |
|  | በእርስዎ አስተያየት ባል በሚከተለው ሁኔታ ሚስቱን ለመምታት ይጸድቃል   1. አዎ 2. አይደለም | | | | | | | | | | | |  |
| 611 | ሳትነግረው ከወጣች? | | | | | 1 | | | 2 | | | |  |
| 612 | ልጆቹን ችላ ካላች? | | | | | 1 | | | 2 | | | |  |
| 613 | ከሱ ጋር ብትጨቃጨቅ? | | | | | 1 | | | 2 | | | |  |
| 614 | ከእሷ ጋር የግብረ ሥጋ ግንኙነት ለመፈጸም ፈቃደኛ ካልሆነች? | | | | | 1 | | | 2 | | | |  |
| 615 | ምግቡን ካቃጠለች? | | | | | 1 | | | 2 | | | |  |
| 616 | **የባህሪ መቆጣጠር ጥያቄዎች** | | | | | | | | | | | |  |
|  | በእርስዎ አስተያየት ባል በሚከተለው ሁኔታ ምስትን በመቆጣጠር ረገድ ትክክል ነው?   1. አዎ 2. አይደለም | | | | | | | | | | | |  |
| 617 | ከሌሎች ወንዶች ጋር ብታወራ መቅናት | | | | | 1 | | | | 2 | | |  |
| 618 | ታማኝነት በማጣት ብከሳት | | | | | 1 | | | | 2 | | |  |
| 619 | ከጓደኞቿ ጋር እንድትገናኝ አለመፍቀድ | | | | | 1 | | | | 2 | | |  |
| 620 | ከቤተሰብ ጋር ያላትን ግንኙነት ለመገደብ መምከር | | | | | 1 | | | | 2 | | |  |
| 621 | የት እንዳለች ለማወቅ ማጥበቅ | | | | | 1 | | | | 2 | | |  |
| 622 | በገንዘብ ባያምናት | | | | | 1 | | | | 2 | | |  |
| 700 | ይህ መጠይቅ ስለ እርስዎ የግል አመለካከት እና ባህሪያት ተከታታይ መግለጫዎች ይዞዋል፡፡ እባኮትን ጠያቂው በሚያነብበት ጊዜ ስለ እያንዳንዱ መግለጫ የራስዎን የግል እምነት ያመልክቱ ይህም የእርስዎን አመለካከት እና ስሜት በተሻለ ሁኔታ የሚገልጽ ነው  1. በፍፁም እውነት አይደለም  2. እምብዛም እውነት  3. መጠነኛ እውነት  4. በትክክል እውነት | | | | | ምርጫዉን አክብቢ | | | | | | |  |
| 701 | በቂ ጥረት ካደረግኩ ሁል ጊዜ አስቸጋሪ ችግሮችን መፍታት እችላለሁ | | | | | 1 | | 2 | | 3 | | 4 |  |
| 702 | አንድ ሰው የሚቃወመኝ ከሆነ የምፈልገውን ለማግኘት ስልቶችን እና መንገዶችን ማግኘት እችላለሁ | | | | | 1 | | 2 | | 3 | | 4 |  |
| 703 | በአላማ ላይ መጽናትና እና ግቦቼን ማሳካት ለእኔ ቀላል ነው | | | | | 1 | | 2 | | 3 | | 4 |  |
| 704 | ያልተጠበቁ ክስተቶችን በብቃት ማስተናገድ እንደምችል እርግጠኛ ነኝ | | | | | 1 | | 2 | | 3 | | 4 |  |
| 705 | ለሀብቴ ምስጋና ይግባውና ያልተጠበቁ ሁኔታዎችን እንዴት እንደማስተናግድ አውቃለሁ | | | | | 1 | | 2 | | 3 | | 4 |  |
| 706 | አስፈላጊውን ጥረት ካደረግኩ ብዙ ችግሮችን መፍታት እችላለሁ | | | | | 1 | | 2 | | 3 | | 4 |  |
| 707 | ችግሮች ሲያጋጥሙኝ መረጋጋት እችላለሁ ምክንያቱም በመቋቋም ችሎታዬ መታመን እችላለሁ | | | | | 1 | | 2 | | 3 | | 4 |  |
| 708 | ከችግሩ ጋር ሲያጋጥመኝ ብዙ መፍትሄዎችን ማግኘት እችላለሁ | | | | | 1 | | 2 | | 3 | | 4 |  |
| 709 | ችግር ካጋጠመኝ, ብዙውን ጊዜ መፍትሄውን ማሰብ እችላለሁ | | | | | 1 | | 2 | | 3 | | 4 |  |
| 710 | ብዙውን ጊዜ በመንገዴ የሚመጣውን ማንኛውንም ነገር መቋቋም እችላለሁ | | | | | 1 | | 2 | | 3 | | 4 |  |
|  | **ክፍል ሰባት : ከዚህ በፊት በነበራቸዉ እርግዝና ውስጥ የቅርብ አጋር(ባል) ጥቃት በተመለከተ** | | | | | | | | | | | | |
| 801 | **አካላዊ ጥቃት**  በቅርብ እርግዝና ወቅት, የትዳር ጓደኛዎ : | 1.አዎ 2. አይደለም  በጥፊ መትተዋሉ ወይም ሊጎዳህ የሚችል ነገር ወርውሮቦታል ?..1 2  ገፍትሯሉ፣አናዉጠዋሉ ወይም ፀጉሮትን ጎትተዋሉ……..1 2  በጥፊ ወይም በሌላ ሊጎዳዎት በሚችል ነገር መትተዋሉ?.,.1 2  መትተዋሉ፣ ጎትተዋሉ ወይስ ደብድበዋሉ?....................1 2  ሆን ብለዉ እርሶን ለማፈን ወይም ለማቃጠል ሞክረዋሉ?..1 2  በእርሶ ላይ ሽጉጥ፣ ቢላዋ ወይም ሌላ መሳሪያለመጠቀም ወይም በትክክል ለመጠቀም አስፈራርተዋሉ?....................1 2 | | | | | | | | | | |  |
| 802 | **ስነ-ልቦናዊ**  በቅርብ እርግዝና ወቅት, የትዳር ጓደኛዎ ፣ | 1.አዎ 2. አይደለም  እርሶን በሌላ ሰው ፊት ለማዋረድ አንድ ነገር ለመናገር  ሞክረዋሉ ወይስ ተናግረዋሉ?.................................1 2  እርስዎን ወይም እርስዎን የሚንከባከቡትን ለመጉዳት አስፈራርተዋሉ?………………………..……..1 2  ሰድቦዋሉ ወይም እርሶ መጥፎ ስሜት እንዲሰማ አድርገዋሉ?………………….…………………1 2  ሆን ብለዉ ማንቋሸሽ ወይም ማስፈራራት  አድርገዋል (ለምሳሌ፡ በአመለካከት  በመጮህ እና ነገሮችን በመሰባበር)?.........................1 2 | | | | | | | | | | |  |
| 803 | **ወሲባዊ**  በቅርብ እርግዝና ወቅት, የትዳር ጓደኛዎ | 1.አዎ 2. አይደል  እረሶ ሳይፈልጉ በጉልበት ወሲብ  ለመፈጸም አስገድደዋሉ?........................................1 2  በጉልበት በማስፈራራት ወይም በሌላ በማንኛዉም  መንገድ ሳይፈልጉ ወሲብ ፈጽመዋል?...................1 2  እርሲ ሳይፈልጉ በጉልበት ሌላ የወሲብ  ንክክዎችን እንድፈጽሙ አድርገዋሉ?……….…....1 2 | | | | | | | | | | |  |
| 804 | ከሶስቱ (801፣802እና 803) ብያንስ አንዱ አዎ ከሆነ፣ ምን አደረጉ? | ምንም…………………………………………………………..1  ለጓደኞቹ አመልክተዋሉ……………………………………..........2  ግንኙነት ማቋረጥ……………………………………………...…3 | | | | | | | | | | | ምንም ከሆነ ወደ 805 እለፊ |
| 805 | ምንም ካላደረጉ(ጥያቄ 804(1))፣ለምን | 2. አዎ 2. አይደለም  ሁኔታው አላግባብ የመሆኑ እርግጠኛ አለመሆን ……....1 2  ፍርሃት……………………………………………….1 2  ይቅርታ አልኩት……………………………………....1 2  ማፈር እና መሸማቀቅ…………………….………..,,..1 2 | | | | | | | | | | |  |

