**Factors associated with IPV**

Individual, family, community, and societal factors are related to IPV in pregnancy. Risk factors for intimate partner violence during pregnancy are often almost similar to risk factors for intimate partner violence in general (Al Shidhani et al., 2020; Alebel et al., 2018; Ashenafi et al., 2021; Kiranmai Devineni et al., 2018).

Maternal and male partners' ages have been associated with experience with IPV. Mothers under the age of 30 were at risk of partner violence in the EDHS analysis report (Chernet and Cherie, 2020).

Several factors have been reported as factors associated with IPV. In Sokoto, Northwest Nigeria, it has been found that partner alcohol consumption is significantly associated with the experience of intimate partner violence in pregnancy. In this study, pregnant women whose partners consume alcohol are more likely to experience IPV during pregnancy compared to those whose partners do not consume alcohol (Oche et al., 2020). Similarly, a cross-sectional study conducted among pregnant women in Ofla District, Ethiopia, found that women with alcoholic partners are more likely to experience intimate partner violence in pregnancy compared to women with non-alcoholic partners. This is supported by a cross-sectional study by Testa et al. (2020) in Ambo District, Ethiopia. Women whose partner takes alcohol were more likely to experience intimate partner violence compared to women whose partner doesn’t take alcohol (Tesfa et al., 2020). Pregnant women whose husbands drank alcohol were three times more likely to experience IPV compared to pregnant women whose husbands did not drink alcohol in a cross-sectional study conducted in Bale Zone, South West Ethiopia (Lencha et al., 2019).

In a study done by Luhumyo et al. (2020) in Eldoret, Kenya, it was revealed that lower than tertiary education level is significantly associated with experience of psychological intimate partner violence. Women with lower than tertiary educational levels are more likely to experience intimate partner violence compared to their counterparts with tertiary education (Luhumyo et al., 2020). In an analysis from the 2016 Ethiopia Demographic and Health Survey by Chernet and Cherie (2020), it was found that the primary and secondary educational level of the mothers was the predictor of intimate partner violence in Ethiopia (Chernet and Cherie, 2020).

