**6.6.2 Independent or ecological model variables**

**Individual**: wife age, wife age at marriage, spousal age difference, educational status of couple, occupation of couples, woman’s parity, alcohol use, sex of previous children, birth order smoking, previous ANC and place of delivery.

**Relational:** marriage type, duration of marriage, disparity in education level

**Community**: presence of social support and inequitable gender norms

**Societal**: household wealth index

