| 116 | Does your husband currently drink alcohol? | | | Yes………………...………………………….....1  No………………...………………………….......2 | | | | | | | | | | | | | | | | |  | |
| 117 | How many wives does your husband currently have? | | | One ……………...………………………...….....1  Two and above……………...……………...........2 | | | | | | | | | | | | | | | | |  | |
|  | **PART TWO: Household Variables** | | | | | | | | | | | | | | | | | | | |  | |
| 201 | What type of house does this household have? | | | | | Corrugated iron sheet house-----1  Grass roof house------------------2 | | | | | | | | | | | | | | |  | |
| 202 | Do you have separate room for sleeping? | | | | | 1.yes | | 2.No | | | | | | | |  | | | | | If no go to Q204 | |
| 203 | If yes for Q202, how many rooms? | | | | | 1.One | | 2. Two | | | | | | | | 3.Three | | | | |  | |
| 204 | Do you have a separate room for animals? | | | | | 1.yes | | 2.No | | | | | | | |  | | | | |  | |
| 205 | Do you have a separate room which is used as a kitchen? | | | | | 1.One | | 2. Two | | | | | | | |  | | | | |  | |
| 206 | Does any member of this household own cows? | | | | | 1. Yes | | 2. No | | | | | | | | If yes, how many? | | | | |  | |
| 207 | Does any member of this household own oxen? | | | | | 1. Yes | | 2. No | | | | | | | | If yes, how many? | | | | |  | |
| 208 | Does any member of this household own calves? | | | | | 1. Yes | | 2. No | | | | | | | | If yes, how many? | | | | |  | |
| 209 | Does any member of this household own other cattle? | | | | | 1. Yes | | 2. No | | | | | | | | If yes, how many? | | | | |  | |
| 210 | Does any member of this household own horses? | | | | | 1. Yes | | 2. No | | | | | | | | If yes, how many? | | | | |  | |
| 211 | Does any member of this household own donkeys? | | | | | 1. Yes | | 2. No | | | | | | | | If yes, how many? | | | | |  | |
| 212 | Does any member of this household own mules? | | | | | 1. Yes | | 2. No | | | | | | | | If yes, how many? | | | | |  | |
| 213 | Does any member of this household own sheeps? | | | | | 1. Yes | | 2. No | | | | | | | | If yes, how many? | | | | |  | |
| 214 | Does any member of this household own goats? | | | | | 1. Yes | | 2. No | | | | | | | | If yes, how many? | | | | |  | |
| 215 | Does any member of this household own chickens? | | | | | 1. Yes | | 2. No | | | | | | | | If yes, how many? | | | | |  | |
| 216 | Does any member of this household own beehives? | | | | | 1. Yes | | 2. No | | | | | | | | If yes, how many? | | | | |  | |

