| 233 | How many quintals of the following legume do the family produced in this year? | | | | | 1.Bean  --------  2.pea  -------- | | | | 3. Lentil  -------  4.Nut  ------- | | | | | | 5. Chick pea  --------  6.grass pea  -----------  7.others,pecify | | | | |  | |
| 234 | How many kilograms of vegetables do the family produced? | | | | | 1.Gomen  2.Carrot  3.Potato | | | | 4. Tomato  5. Cabbage  6. Onion  10. Garlic | | | | | | 7.Beat root  8. Pumpkin  9.Pepper  11.Other specify | | | | |  | |
| 235 | How many kilograms of fruits do the family produced? | | | | | 1.Mango 2.Banana  3.Avocado | | | | 4. Papaya  5. Guava  6.Lemon | | | | | | 7. Other specify- | | | | |  | |
|  | **PART THREE: History of recent pregnancy and delivery** | | | | | | | | | | | | | | | | | | | | | |
| 301 | How many live births have you had? | | Enter number……………………………….. | | | | | | | | | | | | | | | | |  | | |
| 302 | Did you attend ANC for your recent pregnancy from skilled health personnel (nurse, mid-wife, and doctor or health officer)? | | Yes………………………….……………..….1  No……………………………………………..2 | | | | | | | | | | | | | | | | | If ‘**no**’  Skip to  **306** | | |
| 303 | If yes, where did you attend? | | Hospital..............................................................1  Health center…..................................................2  Health post/ clinic..............................................3  Home..................................................................4 | | | | | | | | | | | | | | | | |  | | |
| 304 | How many months pregnant were you when you first received antenatal care for the recent pregnancy? | | Enter the number months/weeks……………… | | | | | | | | | | | | | | | | |  | | |
| 305 | Has your baby’s father attended any antinatal visits with you for the most recent pregnancy? | | Yes……………………………….……………1  No………………….………………………….2 | | | | | | | | | | | | | | | | |  | | |
| 306 | Where did you deliver your recent baby? | | Hospital...........................................................1  Health center……….………………………….2  Health post/clinic……..……………………….3  Home…………….…………………………….4 | | | | | | | | | | | | | | | | |  | | |
| 307 | If it is at hospital or health center or health post/clinic, was the husband/partner present during labor or delivery? | | Yes ….………………………………………...1  No …………………………….………………2 | | | | | | | | | | | | | | | | |  | | |
|  | **PART FOUR: HISTORY OF CURRENT PREGNANCY** | | | | | | | | | | | | | | | | | | |  | | |

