***ባህሪያዊ***

- ብዙ የሴት ጓደኛ መኖር
- በእረግዝና ወቅት አስካሪ መጠጥ/አልኮል መዉሰድ
- በእርግዝና ወቅት ማጨስ
- ጫት መቃም
- በግዜ የቅድመ-ወሊድ ክትትል አለማድረግ

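### The Amharic women's form asks only about areke and beer where the planned variable is alcohol use, and the annexed husbands' forms carry no alcohol item to make up for it

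*Protocol*

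**What the plan says.** Section 6.6.2 gives the individual-level variables as including "alcohol use, sex of previous children, birth order smoking". No beverage is named. The English women's form (Annex II, Part One, item 116) asks "Does your husband currently drink alcohol", answered yes or no.

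The Amharic women's form (Annex VI, Part One, item 115; the numbering differs by one because the Amharic form has no family income item) asks "ባሎት/የትዳር አገርዎ በአሁኑ ጊዜ አረቄ /ቢራ ይጠጣል". This asks whether the husband or partner currently drinks areke (a spirit) or beer. The answers are yes and no, with no option for other drinks and no follow-up question.

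Section 6.21 describes the husbands' questionnaire as covering current alcohol use. The English husbands' form (Annex III) and the Amharic one (Annex VII) both end their background part with the number of wives, go on to knowledge, and contain no alcohol question.

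The Amharic handout (Annex IX, behavioural consequences) uses a general expression, "በእረግዝና ወቅት አስካሪ መጠጥ/አልኮል መዉሰድ", which refers to taking intoxicating drink or alcohol during pregnancy.

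**The concern.** The two language versions of one item define different exposures. A woman whose husband drinks only something other than areke or beer answers yes to the English item and, on a literal reading, no to the Amharic one. Because the annexed husbands' forms do not ask about drinking, no second measure is available to correct the first.

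Partner drinking recurs as a risk factor in the protocol's own literature review, which reports from one Ethiopian study that "Pregnant women whose husbands drank alcohol were three times more likely to experience IPV". Specific Objective 1 (Section 5.3.2) is to assess the prevalence of violence in pregnancy and its associated factors. Counting some drinkers as non-drinkers mixes exposed couples into the unexposed group, which pulls the estimated association towards the null. It also makes alcohol a poorer variable for the baseline comparison planned in Section 6.24, or for adjustment if it is used in that way.

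**Working it through.** **Comparison of the instruments**

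| Place | What is asked or planned |
|---|---|
| Section 6.6.2 | Alcohol use, unrestricted |
| Annex II, item 116 (English, women) | Alcohol in general |
| Annex VI, item 115 (Amharic, women) | Areke or beer |
| Section 6.21 (husbands' questionnaire, as described) | Current alcohol use |
| Annex III (English, husbands) | No alcohol item |
| Annex VII (Amharic, husbands) | No alcohol item |
| Annex IX (Amharic handout) | General term for intoxicating drink or alcohol |

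The Amharic item is narrower than both the planned variable and its English source. The handout shows that the language did not force this.

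**Who can be misclassified.** Only husbands who drink alcohol but neither areke nor beer. A man who drinks either of these as well as something else is still coded yes. False positives are not expected, so specificity is taken as 1.

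**Illustration of size.** The protocol states no figure to reproduce. Inputs:

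- Overall prevalence of violence, 37.5%: from the sample size section (6.8).
- True odds ratio of 3: an assumption, prompted by the threefold figure in the literature review.
- Share of husbands who drink, q = 40%, 50% or 60%: an assumption.
- Sensitivity of the item, s = 95%, 90%, 80% or 60%: an assumption.

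Step 1. Find the risk in drinkers (p1) and in non-drinkers (p0) from q·p1 + (1 − q)·p0 = 0.375 and [p1/(1 − p1)] / [p0/(1 − p0)] = 3. For q = 50% this gives p1 = 0.50 and p0 = 0.25. Check: 0.5 × 0.50 + 0.5 × 0.25 = 0.375, and 1 / (0.25/0.75) = 3.

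Step 2. Move the missed drinkers, q(1 − s), into the unexposed group. Its risk becomes u = [(1 − q)·p0 + q(1 − s)·p1] / [(1 − q) + q(1 − s)]. For q = 50% and s = 80%: u = (0.125 + 0.05) / (0.5 + 0.1) = 0.175/0.6 = 0.2917.

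Step 3. Observed odds ratio = [p1/(1 − p1)] / [u/(1 − u)]. In the same case: 1 / (0.2917/0.7083) = 2.43.

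Repeating this over the grid:

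| Sensitivity | 40% drinkers | 50% drinkers | 60% drinkers |
|---|---|---|---|
| 95% | 2.88 | 2.82 | 2.73 |
| 90% | 2.77 | 2.67 | 2.53 |
| 80% | 2.59 | 2.43 | 2.24 |
| 60% | 2.32 | 2.11 | 1.90 |

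The loss is small if few husbands drink only other beverages and substantial if many do. The documents do not say which applies.

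**The case against.** Five counter-arguments deserve weight.

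*The Amharic form may not be the one used in the field.* Sections 6.16 and 6.21 say the questionnaire goes into Hadiyisa; only Section 6.22 names Amharic. Interviewers must speak both languages (Section 6.18), and no Hadiyisa form is annexed. This stands, and it makes the point conditional on use of the Amharic form. It does not remove the point, because the Amharic form is the only translation shown.

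*The planned translation check should catch the error.* Section 6.16 provides for blinded back-translation, item-by-item scoring against the English, an expert committee and a pilot in 27 couples. That comparison is aimed at this kind of mismatch. The document does not show whether the annexed text had already passed it, so correcting the item now is consistent with the planned process.

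*Respondents may hear areke and beer as everyday shorthand for drinking.* Possibly. The documents cannot settle it. It would reduce the size of the problem but would not make the wording right.

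*Section 6.21 promises a husband's own report.* If that is honoured, a second measure exists. As annexed, neither husbands' form delivers it, which is an inconsistency to resolve in its own right.

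*Alcohol is a covariate, worded identically in both arms, and Section 6.24 names no adjustment for it.* This stands and limits the reach of the point.

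A reader comparing the forms might also infer that the previous-ANC item is defective, because the English item asks "Did you attend ANC for your recent pregnancy from skilled health personnel" while the Amharic asks "ከዚህ በፊት ለነበረዉ የቅርብ ጊዜ እርግዝና የቅድመ ወሊድ ክትትል አድርገዉ ነበር" with no provider qualifier. The documents do not support that as a failure to measure the planned variable. Section 6.6.2 lists previous ANC without any qualifier, and Amharic item 303 goes on to record where the care was received.

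**Conclusion.** The mismatch is established by the text: Amharic item 115 measures drinking of areke or beer, not alcohol use, and no other annexed form measures alcohol at all. The consequence is conditional. It arises where the Amharic form is used, the item is answered literally, and the husband drinks only other alcoholic drinks.

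Under the stated assumptions a true odds ratio of 3 would be seen as about 2.9 to 2.7 at 95% sensitivity, falling to 2.3 to 1.9 at 60%. These figures illustrate direction and range. They are not an estimate of the loss, because the share of husbands who drink only other beverages is not given.

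A reader might infer that the trial's result on violence is biased. The documents do not support that: alcohol is not an outcome, and the same wording applies in both arms, so the randomised comparison is not biased by it. What is affected is the associated-factors analysis under Objective 1 and any use of alcohol as a baseline or adjustment variable. This is a modest measurement point that is cheap to correct.

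**What to change.** 1. Reword Amharic item 115 to ask about any alcoholic drink, using the general term already in the Amharic handout (አስካሪ መጠጥ/አልኮል), with areke and beer as examples.
2. Check the same item in any Hadiyisa version during the back-translation comparison in Section 6.16, and state which language version is used in the field, since Sections 6.16 and 6.21 differ from Section 6.22.
3. Reconcile Section 6.21 with the husbands' forms: either add a current alcohol use item to Annexes III and VII, or remove it from the description.

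The cost is one reworded question and, if the description is kept, one added question on the husbands' form, both before the 27-couple pilot. No extra participants, visits or staff are needed. If the Amharic form has already been used as annexed, report the variable as areke or beer drinking and state the limitation.
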